#### Experimental group: PVB

Three single injections, awake or asleep, using a 16 G/18 G graduated epidural needle with 15 mL 0.25% bupivacaine at T3–4, 5–6 and 7–8, will be given preoperatively. The PVB catheter will be placed at T5 under direct vision by a surgeon at the end of surgery before chest closure. A loading dose of 10 mL 0.25% bupivacaine is given before chest closure followed by infusion of 0.125% bupivacaine 0.1–0.25 mL/kg/hour. See online supplementary appendix for further details.

10.1136/bmjopen-2016-012735.supp1Supplementary appendix

#### Control group: TEB

Usual practice of TEB, awake or asleep, using a 16 G/18 G graduated epidural needle with a catheter inserted at the spinal level supplying the skin at the incision site, a test dose of 3 mL of 0.25% bupivacaine, and a loading dose of 0.25% bupivacaine 0.1 mL/kg with up to 3 mg of diamorphine. This will be followed by infusion of 0.125% bupivacaine with 2 μg/mL fentanyl at 0.1–0.25 mL/kg/hour. See online supplementary appendix for further details.

#### Study treatment dispensing

All anaesthetics and analgesia will be taken from standard theatre pharmacy stock. As TOPIC does not fall under the Medicines for Human Use (Clinical Trials) regulations 2004, segregated stocks for trial use and specific trial labelling are not required. Temperature monitoring should follow local pharmacy practice and deviations need not be reported to the TOPIC Study Co-ordinator.

#### Blinding of trial allocations

By the nature of the interventions, it is not possible to conceal treatment assignments from surgeons and anaesthetists. Moreover, from a safety aspect, it is vital that the nursing staff caring for the patient know the amount of epidural opiates prescribed before administering systemic opiates, and known adverse events such as hypotension or pruritus expected to arise from the respective anaesthetic approaches.

Every attempt will be made to blind study participants to their group allocation. The epidural or PVB infusion catheter will be taped laterally on the side of operation, so no visible difference can be seen by the patient. Infusion pumps used by both groups will also be identical.

#### Withdrawal from the trial

Withdrawal from the trial before surgery is a decision of the participant; however, withdrawn patients can bias trial results and reduce the power of the trial to detect important differences, so randomisation will take place as close to the time of surgery as is practical in order to reduce postrandomisation withdrawals. Following surgery, participants should be encouraged to allow clinical data collection to continue even if they decline to complete further questionnaires.

Cessation of the allocated anaesthetic strategy will also be necessitated in cases where a known serious adverse reaction to the anaesthetic occurs or a suspected unexpected serious adverse reaction occurs.

#### Protocol violations

Any incidences of study participants not receiving the anaesthetic strategy allocation by randomisation will be recorded. All study and protocol violations and deviations will be documented in the patients CRF and reported to the Study Sponsor via the Trial Office. Patients will be analysed according to group allocation, by intent-to-treat analysis.

#### Additional intraoperative analgesia

Supplementary intraoperative analgesia will not be restricted and can follow local policy. Analgesia and doses will be recorded as part of the study in the patients CRF.

#### Postoperative analgesia

Both groups should continue with TEB/PVB infusion of 0.1–0.25 mL/kg/hour bupivacaine, in the first instance for 48 hours postoperatively. All participants will receive regular paracetamol and prophylactic antiemetics unless contraindicated. Non-steroidal anti-inflammatory drugs can also be administered if appropriate. All analgesic requirements will be recorded during inpatient follow-up.

For the TEB group, intravenous morphine boluses will be prescribed for breakthrough pain which is not relieved by the epidural top ups. If the epidural is ineffective and no block is evident, the TEB can be reinserted at the discretion of the anaesthetic team. If pain relief is inadequate, morphine PCA (patient-controlled analgesia) can be administered.

For the PVB group, intravenous morphine boluses followed by morphine PCA will start on recovery from anaesthesia.

## Outcomes and data collection

### Patient recruitment into study

The overall aims of the feasibility are to find out if a larger trial is feasible. The quantitative measurements related to this include
proportion of all elective thoracic procedures screened,proportion of eligible participants of those screened,proportion of eligible participants randomised.

In this feasibility study of two centres, HEFT and University of south Manchester NHS Foundation Trust, there would be an approximate total of 500 elective open thoracotomies over the study period. The plan will be to recruit and randomise as many patients as possible over the 12-month study period. It is expected that between 50 and 75 eligible patients will be recruited from 2 sites.

### Patient identification and screening

We would expect a very high proportion of patients to be screened across both study sites, given that only patients with planned thoracotomy will be included. The proportion of patients screened for eligibility and recorded on a screening log will be assessed and reported as proportion of patients screened from the total number of planned thoracotomies during the study period.

### Reasons for failure to recruit

The proportion of patients that were missed, which should be minimal, and the proportion of patients who decline to take part will be recorded. Patients decline for many reasons, which should be captured whenever possible. We will consent declining patients to a short interview. The reasons for declining will be recorded anonymously and analysed by the research team. If there is a strong patient preference, the substantive trial may not be feasible, similarly if this population is disinterested or conversely, taking part in other trials that preclude concurrent participation.

### Educational materials and training of surgeons and anaesthetists

Feedback on the appropriateness, value and acceptability of the training will be elicited from the feasibility sites, to enable refinement of the training programme for the substantive study, and to define a minimum competence. The training material will be evaluated for its ease of use should it be used in the substantive study.

### Evaluation of willingness of anaesthetists and surgeons to participate

As part of preparation of the study site, all anaesthetists and surgeons in both sites will be approached to evaluate willingness to participate in the trial. The Site PI(s) and the trial coordinator will discuss the protocol to ensure that all inclusion/exclusion criteria and technical aspects are well understood by the participating anaesthetists and surgeons. Patient ‘vignettes’, typical and unusual, will be presented during this training to establish whether uncertainty exists and therefore randomisation is ethical in all situations, or whether there are somewhere either technique is preferred. Training material will be revised, as per the feedback for use in the substantive study, portraying best practice in approaching and consenting participants.

The study team will also conduct a repeat national survey to assess willingness from the clinical community nationally towards the end of feasibility study.

### Effectiveness of randomisation process

This would be ascertained by the speed in which patients can be randomised and whether important prognostic data can be collected preoperatively.

### Assessment of data collection process

Assessment and identification will be made for loss of data during inhospital stay to improve data collection process for the substantive trial.

### Assessment of sustainability of single blinding of patients to treatment allocation

By the nature of the interventions, it is not possible to conceal treatment assignments from surgeons and anaesthetists. Every attempt will be made to blind study participants to their group allocation and various methods may be considered. The patient-reported outcomes will be collected remote in time from the acute intervention. There is no reason to suspect that recipients of the randomised intervention have strong preconceptions with regard to the relative effectiveness of each analgesic technique. In this feasibility study, patients will be asked at 3 and 6 months after surgery via questionnaire which technique they think they received to test if our various methods for patient blinding were effective.

### Assessment of follow-up rates

The primary outcome of the substantive study is chronic pain assessed at 6-month postrandomisation. It is therefore vital for the appropriate measures to be in place to minimise the loss of follow-up.

The research team will demonstrate and assist the patient to complete the questionnaires in person when the baseline data are collected. This face-to-face assistance and support in filling the questionnaire will help encourage patients and increase their confidence in completing questionnaires after discharge.

The patient has consented to be contacted by post or by telephone for follow-up purposes. Prior to the follow-up questionnaires being sent to patients at home, their vital status will be confirmed by a research team member from study sites. The contact information and patient status will be faxed from study sites to BCTU for follow-up purposes. Follow-up questionnaire will include pain questionnaires, patient satisfaction questionnaire and assessment of single blinding. To be viable as a primary outcome, we would expect to achieve a response rate of 80% of expected patients, using various methods of contact. We should be able to capture 100% of mortality data via NHS tracing services. A withdrawal from follow-up of over 10% would be disappointing. The reasons for loss of follow-up if any will be documented and reported at the end of the feasibility study.

### Patient-reported outcomes

At baseline and prior to surgery, five sets of questionnaires will be completed. These comprise: Visual Analogue Scale score, Brief Pain Inventory interference score (BPI),^29^
^30^ Neuropathic Pain Scale (NPS),^31^ Generic health-related quality of life (EQ-5D-5L)^32^ and Hospital Anxiety and Depression Scale (HADS).^33^

Inhospital data collection will include Visual Analogue Scale scores, Brief Pain Inventory, analgesic use, any acute complications conducted on day 1, day 2 and day 3 postsurgery. Using day of surgery as day 0, day 1 is defined as the first full calendar day (from 12 midnight) postsurgery, day 2 is the second full calendar day and day 3 is the third full calendar day.

On hospital discharge, take home analgesia (TTOs), inhospital mortality, acute complications, unplanned admission to level 2 or level 3 care, including organ support and length of level 2/level 3 stay and total length of hospital stay. Assessment and identification will be made for loss of data during inhospital stay to improve data collection process for the substantive trial.

Six sets of questionnaires will be completed prior on hospital discharge and at 3 and 6 months postrandomisation. The national registry will be checked to confirm patients status prior to follow-up questionnaires being sent at 3 and 6 months. These questionnaires are Patient satisfaction questionnaire with their overall care and with their pain relief and question to assess whether patient was aware of treatment allocation, Visual Analogue scale scores, BPI,^29^
^30^ NPS,^31^ Generic health-related quality of life (EQ-5D-5L)^32^ and HADS.^33^

### Acceptability to and impact on patients

Patient interviews will explore the acceptability of the intervention to patients and any impacts on their stay in hospital and postdischarge. Semistructured qualitative interviews will be undertaken with up to 30 study patients with representation of patients taking part across the 2 sites. The interviews will be conducted at 6–8 weeks postdischarge. This will allow for a reasonable recovery period postsurgery and will enable interviews to be undertaken with the small proportion of patients who go on to need chemotherapy, prior to this treatment beginning. The interviews will be performed by telephone in order to minimise the disruption to and effort required by patients.

All patients will be eligible for interview and will be selected using maximum variety sampling by age, sex and ethnic group.^34^ The need for a maximum variety sample will be balanced against spacing the interviews as evenly as possible across the 12 months of the trial so that any variations in how the trial is implemented are reflected in the patient sample. Interviews will be conducted until saturation is achieved, which is likely to be around 30 patients.^35^

A framework for the patient interviews will be developed in months 1–3 of the trial set-up period, with reference to the literature on similar trials. The framework will also be discussed with Clinical Research Ambassador Group (CRAG) based within HEFT. It will include five core questions that will be asked of all patients, which will cover:
Reasons for taking part in the trialAssessing whether patients knew which anaesthetic strategy they receivedThe effectiveness of staff and written communication about the trialHow the trial impacted on their stay in hospital and at home following dischargeSuggestions for making improvements to the recruitment processes

The semistructured nature of the interviews will allow patients to raise issues which may not have been anticipated by the research team, and will allow the interviewer to explore any patient concerns in depth. The interviews are expected to last an average of 15–20 min, and will be recorded digitally. If during the interviews, any patients indicate that they have unresolved concerns or clinical symptoms, they will be directed to their named research nurse. Similarly, if patients get upset, the interviewer will ask for the patient's consent to be contacted by their dedicated research nurse for further discussion.

Telephone interviews will also be undertaken with up to 10 patients who declined to take part in the trial, to explore their reasons for declining and to identify how a larger trial could be adapted to encourage higher rates of participation.

### Assessment of trial processes and impact on staff

Semistructured qualitative interviews with clinical and research staff will be undertaken to explore the effectiveness and efficiency of the trial processes. This will include exploring a number of the secondary outcomes:
The effectiveness of the patient identification and screening processesIdentification of reasons for failure to recruit patientsThe willingness of surgeons and anaesthetists to take partThe effectiveness of the randomisation process

Interviews will also ask for staff ideas for improvement in trial processes, and explore whether there are any unintended consequences of the trial procedure which might have an impact on patient care processes or the organisation and management of care.

Up to 20 staff interviews will be undertaken, which will be spread evenly across the two sites and will include the main clinical and managerial roles affected by the trail. The interviews will be undertaken in the month following the discharge of the last trial patient home. The interviews are expected to last an average of 20–30 min, and will be recorded digitally Data Collection and Management.

All data for an individual patient will be collected by each Principal Investigator or their delegated nominees and recorded in the study-specific data collection forms (CRF). Participants will only be identified through their unique trial number allocated at the time of randomisation and their initials. Data will be collected from the time the patient is entered into the trial through their discharge from hospital and up to 6 months postsurgery.

## Statistics and data analysis

### Sample size calculation

We expect to recruit between 50 and 75 patients depending on the number we find eligible for the study. For example, we estimate that there will be ∼500 open elective thoracotomies over 12 months from the 2 sites (HEFT and UHSM), of which 60% will be eligible (300). Using our own target criteria of 25% recruited would make 75 participants. This number will allow us to measure the recruitment rate with 95% CI of width ∼10%. It will also be enough to estimate the SD of VAS score with 95% CI of width 7 points (assuming the SD is around 25 points).

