### Handling missing data

There is a potential for some missing data to occur at follow-up; however, a member of the research team will contact patients for any missing data (eg, questionnaire) via telephone and post. Where patients attend for follow-up clinic, the potential for missing data will again be limited, and the secondary outcome data will also be collected at this point. Imputation of missing responses is not proposed for patient-reported outcome as this is not a definitive trial and no hypothesis testing will be performed

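### With 75 patients and an SD of 25, the 95% confidence interval for the SD of VAS is about 8 points wide, not the stated 7

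*Protocol article*

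**What the plan says.** The protocol's Sample size calculation section opens with a range: "We expect to recruit between 50 and 75 patients depending on the number we find eligible for the study". It then works an example of about 500 elective open thoracotomies in 12 months, 60% of them eligible (300): "Using our own target criteria of 25% recruited would make 75 participants". Two statements of precision follow for those 75. The first concerns recruitment: "This number will allow us to measure the recruitment rate with 95% CI of width ∼10" per cent. The second says that the number will also be enough to "estimate the SD of VAS score with 95% CI of width 7 points (assuming the SD is around 25 points".

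The second statement names no assessment time and makes no allowance for missing scores. Table 1 schedules VAS at baseline, on days 1 to 3, at discharge, and at 3 and 6 months. Three other places bear on how the SD might be used:

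- The last of the Secondary objectives is to obtain preliminary clinical data to inform the sample size of the substantive trial.
- Assessment of follow-up rates says "The primary outcome of the substantive study is chronic pain assessed at 6-month postrandomisation", and for the questionnaires "we would expect to achieve a response rate of 80% of expected patients, using various methods of contact".
- Handling missing data says "Imputation of missing responses is not proposed for patient-reported outcome".

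**The concern.** The second precision statement can be checked from its own inputs: 75 patients, an SD of 25, 95% confidence and a width of 7. The standard interval for an SD at those values is wider than 7. The study plans no hypothesis tests, so its numerical case for size consists of the expected recruitment and these two precision statements, and one of the two is misstated.

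The practical stake is modest. A required sample size for a continuous outcome scales with the square of the SD. A reader who takes the printed width at face value would expect the pilot to pin down the SD, and so the size of the later trial, somewhat better than 75 patients can.

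**Working it through.** **Inputs, all from Sample size calculation unless noted**

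- n = 75 (500 × 0.60 × 0.25)
- s = 25, 95% confidence, stated full width 7
- lower end of expected recruitment: 50
- expected questionnaire response of 80% (Assessment of follow-up rates), so 75 × 0.80 = 60. The 60 is derived; the protocol does not print it.

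**Step 1. Check the companion figure, to fix the conventions.** Wald width for 25% of 300:

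2 × 1.96 × √(0.25 × 0.75 / 300) = 0.098, or 9.8 percentage points.

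This agrees with the stated figure of about 10%. The section is therefore quoting full widths at 95% confidence for the 75-of-300 example.

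**Step 2. Try to reproduce the 7.** Under normality the 95% interval for an SD runs from s√(df/χ²₀.₉₇₅) to s√(df/χ²₀.₀₂₅), with df = n − 1. For df = 74 the quantiles are 99.68 and 52.10:

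- lower limit: 25 × √(74/99.68) = 21.54
- upper limit: 25 × √(74/52.10) = 29.79
- width: 8.25, about 18% above 7

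**Step 3. Try other routes to 7 at n = 75 and s = 25.**

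| Method | Width |
|---|---|
| Large-sample, 2 × 1.96 × 25/√(2 × 74) | 8.06 |
| Large-sample with 2n, 2 × 1.96 × 25/√150 | 8.00 |
| Log-scale normal interval | 8.09 |
| Pooled two-arm SD, df = 73 | 8.31 |
| Chi-square interval at 90% confidence | 6.89 |

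Reading 7 as a half-width does not help: the limits lie 3.5 below and 4.8 above 25. Only the 90% interval rounds to 7. Keeping 95% confidence and n = 75, a width of 7 requires an SD of 25 × 7/8.25 = 21.2.

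**Step 4. Find the n that gives a 95% width of 7.** The chi-square width is 7.02 at n = 102 and 6.98 at n = 103, so 103 patients with VAS data are needed (99 by the large-sample formula). Rounding does not rescue the claim either: a width that merely rounds to 7 (below 7.5) needs 90 patients, which is more than the planned maximum.

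**Step 5. Widths at the other numbers that the protocol implies (chi-square, s = 25).**

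| Patients with VAS data | 95% interval | Width |
|---|---|---|
| 75 | 21.5 to 29.8 | 8.25 |
| 60 (80% of 75) | 21.2 to 30.5 | 9.30 |
| 50 | 20.9 to 31.2 | 10.27 |

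**Step 6. Effect on a later sample size.** The upper limits correspond to (29.79/25)² = 1.42 times the nominal size at 75 patients and (30.49/25)² = 1.49 times at 60.

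**The case against.** The best reply is that this is a one-point discrepancy in a supporting sentence. The 75 comes from 500 × 60% × 25%, and neither precision statement sets it. The primary objective is the proportion of eligible patients randomised, and the precision quoted for that is right. No test or progression rule depends on the SD width, and the actual SD and its interval can be computed from the data when the study ends. All of this stands, and it limits the point to a minor correction. It does not make 7 correct.

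A second reply is that the check assumes normality. The sampling error of an SD depends on kurtosis, and a bounded score can be flatter than normal. As an illustration under assumed beta distributions on a 0–100 scale with SD 25, the large-sample width at n = 75 is about 7.1 when the mean is 30 and about 9.5 when it is 20. The conclusion should therefore be stated as holding under normality. By the same token, a reader might infer that right skew must widen the interval further. That does not follow, since both of those shapes are right-skewed. Nothing in the protocol suggests that the 7 came from a non-normal calculation.

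A third reply is that the sentence ties the SD to no time point, so attrition may be irrelevant. This is also fair. For VAS at baseline or in hospital the relevant width is the one for 75 patients, and it still exceeds 7. The 60-patient figure applies only if the SD is wanted at 6 months. The response rate is also expressed relative to expected patients; if deaths are excluded from that base, the number with data could be below 60.

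**Conclusion.** The stated width is wrong as printed. Under normality, 75 patients with VAS data estimate an SD of 25 with a 95% interval about 8 points wide (8.25 exact, 8.06 large-sample), and a width of 7 needs about 103 patients. A 90% interval labelled as 95% would explain the figure, but that is an inference.

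Three stronger readings are tempting and are not supported:

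- A reader might conclude that the sample size justification as a whole fails. It does not: the recruitment-rate width reproduces, and the target of 75 does not rest on the SD statement.
- A reader might treat the SD as the pilot's main quantitative product. It serves one secondary objective among eleven, and that objective names neither the SD nor VAS.
- A reader might fault the recruitment-rate width at 50 patients. Doing so needs a number of eligible patients other than 300, and the protocol prints none. The 75 case is presented as an example.

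This is a minor correction of one stated figure.

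**What to change.** Replace the SD sentence in Sample size calculation with wording along these lines:

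*With VAS data from 75 patients, an SD of about 25 points would be estimated with a 95% CI of width about 8 points (21.5 to 29.8), assuming approximate normality. With 50 patients the width would be about 10 points. At 6 months, with 80% of 75 responding (60 patients), it would be about 9 points.*

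Alternatively, keep the 7 and relabel it as a 90% interval for 75 patients, if that is what was calculated. Either version should say at which assessment the SD is wanted.

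The cost is a change of wording and a slightly less favourable stated precision. No extra patients are needed, and the recruitment-rate statement stays as it is. How the later trial uses the SD estimate is a matter for that trial's own protocol.
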